# Opposing needling for analgesia and rehabilitation after unilateral total knee arthroplasty: a randomized, sham-controlled trial protocol

**DOI:** 10.1186/s13063-020-04251-z

**Published:** 2020-05-07

**Keywords:** Opposing needling, Total knee arthroplasty, Sham acupuncture, Pain, Protocol

## Abstract

**Background:**

This randomized controlled clinical trial aims to evaluate the efficacy and safety of opposing needling in patients undergoing unilateral total knee arthroplasty (TKA). Opposing needling is one of the special needling methods used in acupuncture and moxibustion therapy. It involves needling acupoints on the contralateral side for pain management. Although, opposing needling is used for pain management in clinics, evidence to support its effectiveness as an analgesic after total knee arthroplasty is scant. We designed a randomized controlled clinical trial to evaluate efficacy and safety of opposing electroacupuncture (EA) in alleviating pain associated with unilateral total knee arthroplasty.

**Methods/design:**

This is a protocol for a randomized controlled patient- and assessor-blinded trial with three parallel arms (A, opposing EA; B, operated side EA; C, sham EA). *Yinlingquan* (SP9), *Yanglingquan* (GB34), *Futu* (ST32), and *Zusanli* (ST36) acupoints are selected for all three groups. In group A, the healthy side will be treated with EA, while the operated side will be administered sham EA. In group B, the operated side will be treated with EA while on the healthy side sham EA will be used. For group C, sham EA will be used on both sides. All patients in the three groups will receive treatment once a day for 3 days. The post-operative pain measured using a visual analogue scale score (including pain while resting and being active) and the additional dose of the patient-controlled analgesic pump after operation will be recorded as the primary outcomes. Secondary outcomes such as knee function and swelling, range of motion (including active and passive range of motion), post-operative anxiety, and acupuncture tolerance will also be assessed.

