#### Dropout criteria

Any participant will be dropped from the study if she or he (1) cannot tolerate acupuncture after operation or cannot complete the study protocol scheduled; (2) cannot continue the acupuncture procedure because of surgical factors; (3) refuses to receive EA or sham EA treatment; (4) shows SAEs; (5) violates the protocol or refuses to follow up.

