##### Electroacupuncture (EA)

Needles (0.30 mm in diameter, 40 mm in length, Hwato Brand, Suzhou Medical Appliance Factory, China) will be inserted vertically into the acupoints through the adhesive pads to a depth of 25–30 mm (Fig. 3). Acupuncturists will twist to achieve and enhance the sensation of needles inserted into the skin around acupoints, such as numbness, heaviness, aches, etc. (known as *De Qi*). Subsequent electrical stimulation (SDZ-V electroacupuncture apparatus, Huatuo brand, Suzhou Medical Appliance Factory, China) will be connected to each needle handle (a connecting wire connects a pair of acupoints, GB34 to ST32 and ST36 to SP9) and a continuous wave of 2 Hz frequency and an intensity of 1 mA will be maintained.

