##### Sham electroacupuncture (Sham EA)

The blunt needle (Fig. 3, 0.30 mm in diameter, 25 mm in length, Hwato Brand, Suzhou Medical Appliance Factory, China) will reach the skin through the adhesive pads without penetrating the skin. The needle handle is rotated three times to simulate the real acupuncture procedure. The sham electrical stimulation apparatus looks like the real one, but with the inner metal wire cut off so no current passes through the connecting wire between the two needle handle (GB34 to ST32 and ST36 to SP9); a continuous wave of 2 Hz frequency and an intensity of 1 mA is applied [31].

During the treatment, the needle handles are rotated on both sides three times per 5 min by acupuncturist.

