### Outcome measures

#### Primary outcome measurement

The main evaluation criterion is pain, which is divided into two parts.

The first part is a visual analogue scale (VAS). The assessment schedule is shown in Table 1. Independent assessors who are not involved in acupuncture treatments will perform the VAS assessments (asking subjects to indicate the intensity of pain at the most painful points while resting and walking). The 0–100 mm VAS is used to evaluate pain intensity, wherein 0 mm denotes painless and 100 mm represents the most intolerable pain [32]. It allows patients to mark their own feelings on the scale as the evaluation score of pain. In addition to evaluating resting pain at 6 h after the operation, the pain in both the resting and active state is measured immediately after treatment on the first to third days after the operation, and assessed at follow-up on the fifth, seventh, and tenth days after the operation.

**Table 1 Tab1:** Schedule of trial enrollment, interventions, and assessments

Items	Enrollment (pre-operative)	Allocation (baseline)	Treatment (post-operative)				Follow-up		
Time point (hour/day)	-1	-1	6 h	1d	2d	3d	5d	7d	10d
Treatment sessions (n)	–	–		1	2	3			
Informed consent	√								
Assessment of eligibility	√								
VAS (resting)		√	√	√	√	√	√	√	√
VAS (active)		√		√	√	√	√	√	√
Additional dose released by PCA pump					√				
HSS score		√				√			√
HAMA score		√				√			√
AROM		√				√	√	√	√
PROM		√				√	√	√	√
COK				√		√	√	√	√
Discomfort and acceptance of EA				√	√	√			
Assessment of blinding method						√			
Postoperative complications and adverse events				√	√	√			

*VAS* Visual Analogue Score, *PCA* patient controlled analgesia, *HSS* hospital for special surgery, *HAMA* Hamilton Anxiety Scale, *COK* circumference of knee, *AROM* active range of motion, *PROM* passive range of motion

The second part is to record any additional doses from the patient-controlled analgesic pump after the operation, and to evaluate it uniformly on the second day after the operation (at 24 h after the first treatment).

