#### Secondary outcome measurements

The secondary outcome measurements are mainly related to rehabilitation after the TKA operation. They include the following.

The knee score of patients will be measured at three time points—the day before operation and on the third and tenth days after the operation—using the Hospital for Special Surgery Knee Score (HSS), commonly used in similar studies. The HSS gives a maximum of 100 points and includes pain (30 points), function (22 points), range of motion (18 points), muscular strength (10 points), deformity (10 points), instability (10 points), and subtractions (three items) [33, 34].

Active and passive range of motion (ROM) of knee joint will be measured by a standard joint protractor measure [35] on the day before the operation and the third, fifth, seventh, and tenth days after the operation.

Based on the ratio of knee circumference on the first day after the operation, the improvement of swelling around the knee joint will be evaluated on the third, fifth, seventh, and tenth days after the operation according to the following formula: (COK on the Xth-COK on the first day after operation) /(COK on first day after operation), where COK is the circumference of the knee at suprapatellar pole20 [20].

The Hamilton Anxiety Scale (HAMA) consists of 14 items, each of which has five levels [36]. In this study, the severity of anxiety in patients will be assessed on the day before the operation, and the third and tenth days after the operation.

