### Statistical analysis

The data in this study will be analyzed using the Statistical Package for Social Science software (SPSS version 22.0, IBM Corp, New York). After data collection, statistical analysis will be performed by a special statistician. Data analysis will be based on the intention-to-treat (ITT) principle [42], considering significance levels < 0.05 as statistically significant.

Continuous data will be represented by mean, standard deviation, median, and interquartile ranges and the categorical data by percentages.

According to whether the data are normally distributed, the analysis of baseline will be performed using a *t*-test or a Wilcoxon rank sum test for continuous data and a chi-squared test or Fisher’s exact test for categorical data. Comparisons among the three groups will be analyzed by one-way analysis of variance (ANOVA) [43]. When the distribution is not normal, nonparametric tests will be used. Thus, the primary outcome will be assessed using a one-way, repeated-measures ANOVA to test the influence of the time, the group, and the time*group interaction on pain. Comparisons of categorical data among groups will be tested by the chi-square test or the Mann Whitney U-test.

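### Patients who cannot tolerate or who refuse the needling are dropped from the study, so day 2–3 tolerance scores can come from a selected group

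*Protocol article*

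**What the plan says.** The abstract (Methods/design) includes tolerance in its list of secondary outcomes: "post-operative anxiety, and acupuncture tolerance will also be assessed". The section Secondary outcome measurements opens with "The secondary outcome measurements are mainly related to rehabilitation after the TKA operation" and then describes the HSS score, range of motion, knee swelling and the HAMA. It neither lists nor defines tolerance.

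The only matching item is in Table 1, under Primary outcome measurement: "Discomfort and acceptance of EA". It is ticked on post-operative days 1, 2 and 3, the days of sessions 1, 2 and 3, and at none of the follow-up visits on days 5, 7 and 10.

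Under Dropout criteria, a participant leaves the study under criterion 1 if she or he "cannot tolerate acupuncture after operation or cannot complete the study protocol scheduled", and under criterion 3 if she or he "refuses to receive EA or sham EA treatment". The Statistical analysis section states: "Data analysis will be based on the intention-to-treat (ITT) principle".

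**The concern.** Inability to tolerate the needling, and refusal of it, are the clearest poor results a tolerance outcome can have. The dropout rule takes exactly those patients out of the study, while the scheduled measure continues on days 2 and 3 in those who remain. The later scores can then improve as more patients fail to tolerate treatment.

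The comparison of tolerance between arms is at stake. An arm that loses more intolerant patients can look as well tolerated as one that loses none. The Discussion argues that needling the unoperated leg is more acceptable to patients. If the trial's tolerance data are to speak to that, stops for intolerance have to be visible in the result. The primary outcomes (VAS pain and additional PCA dose) are not the subject of this point.

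**Working it through.** The article gives no tolerance figure to reproduce, so the check is mainly a comparison of its sections, followed by an illustration.

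**Sections side by side**

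1. *Outcome.* Tolerance is named in the abstract and undefined in the secondary outcome section.
2. *Measurement.* There is one item, on the three treatment days only. A score for the discomfort of a session needs a session, so a patient who stops after session 1 can have a day 1 score but no session discomfort on days 2 or 3. This follows from the timing in Table 1; the article does not state it.
3. *Dropout.* Criteria 1 and 3 remove the patient from the study, not only from further needling.
4. *Can dropouts be counted instead?* Not cleanly. Criterion 1 joins intolerance to any other failure to complete the schedule, so a tally by criterion would not isolate intolerance.
5. *ITT.* This keeps patients in the arm to which they were allocated. It cannot supply scores for sessions that did not take place.

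**Illustration**

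Inputs from Sample size: 96 patients before dropout, so 96/3 = 32 per arm; a 15% dropout allowance; 38 per arm. The dropout step reproduces: 32/(1 − 0.15) = 37.6, rounded up to 38. The whole allowance applied to 38 patients is 38 × 0.15 = 5.7, taken as 6.

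Assumptions, not in the article: acceptance is scored yes or no; every stop for intolerance comes after session 1; everyone still treated accepts. For *s* such stops in an arm of 38:

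- Acceptance among those still treated = (38 − s)/(38 − s) = 100%, whatever *s* is.
- Acceptance among all randomised = (38 − s)/38.

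| Stops for intolerance | Still treated | All randomised | Gap |
|---|---|---|---|
| 2 | 36/36 = 100% | 36/38 = 94.7% | 5.3 points |
| 6 | 32/32 = 100% | 32/38 = 84.2% | 15.8 points |

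If one arm had 6 such stops and another had 2, both would read 100% among those still treated, while the difference over all randomised would be 94.7 − 84.2 = 10.5 points. If both had 6, both would read 84.2% over all randomised, the difference would be zero on either basis, and neither arm would gain.

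**The case against.** Four arguments carry weight on the other side.

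*A reader might infer that tolerance is measured only in those who tolerate.* The documents do not support that. A patient who stops after session 1 can be scored on day 1. Refusal is a named dropout reason. Blinded observers record acupuncture-related adverse events (EA safety and adverse events). Acceptance, unlike discomfort, could be recorded on a day when the patient declines. The signal is not wholly lost. Even so, the article does not provide for scoring a patient who has been dropped, and the mixed wording of criterion 1 weakens any count made from dropouts.

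*A reader might infer that the true EA arms are favoured.* True EA penetrates the skin and, in the plan's words, "an intensity of 1 mA will be maintained", whereas the sham needle "will reach the skin through the adhesive pads without penetrating the skin" and no current passes. A difference in intolerance from sham is plausible. But the article gives no intolerance rates by arm, criterion 3 itself foresees refusal of sham, and every arm receives sham on at least one leg. Nor does the contrast between true and sham EA bear on opposing against operated-side EA, where the true EA procedure is the same and only the leg differs. The direction is unknown.

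*The size is constructed.* This is correct. The 15% is an all-cause allowance, and the dropout criteria also cover surgical factors, severe adverse events, protocol violation and refused follow-up. Six of 38 is therefore an upper bound within the plan's own allowance and not an expectation.

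*Scoring after a stop belongs in an analysis plan.* How to treat missing scores may well be set out in a document not shown. The point here is different: a stated dropout rule acts on a stated outcome, and the reason for stopping must be captured when it happens. An analysis plan cannot recover it later.

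**Conclusion.** The point holds in limited form. The plan names tolerance as a secondary outcome, schedules its only measure on the treatment days, and drops patients from the study for intolerance or refusal. The day 2 and day 3 scores can therefore come from a selected group and can flatter whichever arm loses more intolerant patients.

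The size cannot be known from the article. The overstatement within an arm would be about 5 points with 2 stops in 38 and about 16 points with 6, under the assumptions of a yes/no score, stops after session 1 and full acceptance among the rest. No direction between arms can be claimed. This is a worthwhile correction to a secondary outcome and does not touch the validity of the primary comparison.

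**What to change.** - Define tolerance in Secondary outcome measurements and report it by arm over all randomised patients.
- Count as not tolerated, from that day on, any stop for intolerance, for refusal of EA or sham EA, or for an adverse event related to the needling. Show refusals before session 1 separately.
- Record the reason for stopping in the case report form, so that intolerance is kept apart from the other non-completion covered by criterion 1.
- Present the day 1–3 discomfort scores descriptively, with the number still treated in each arm on each day.

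The cost is one definition and one field on the form. The downside is that reported tolerance becomes slightly less favourable. No treatment or stopping rule changes, and the analysis of the primary outcomes is unchanged.

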**Discussion:**

Opposing needling is a potential non-pharmacological treatment for relieving pain and improving functional rehabilitation after TKA, during which patients receive acupuncture on the healthy side rather than on the operated side. This sham controlled clinical trial, designed to evaluate efficacy and safety of opposing needling for patients after TKA, will provide evidence for pain management and functional rehabilitation after unilateral TKA.

**Trial registration:**

ChiCTR, ChiCTR1800020297 (http://www.chictr.org.cn/edit.aspx?pid=34231&htm=4). Registered 22 December 2018.

## Background

Total knee arthroplasty (TKA) is one of the best treatments for advanced knee osteoarthritis (KOA) [1], providing a standardized treatment for relieving pain, remodeling knee function, improving quality of life, and improving postural balance [2, 3]. Although a number of benefits are associated with TKA, it is imperative to address the potentially increased rate of complications of post-operative pain, post-operative infection, and deep vein thrombosis among these older patients [4]. The management of post-operative pain is a recurring problem that needs effective rectification. Post-operative pain still accounts for 14.1% of the most common reasons for re-admission within 90 days of surgery as reported in a European study [5]. Thus, post-operative pain is still a major complication that arises after TKA [6]. A number of patients are dissatisfied with the efficacy of commonly used analgesics post-operation and the ancillary side effects that come with them [7, 8]. Kim et al. have focused on the risk factors associated with persistent chronic opioid usage after surgery and suggest that targeted opioid reduction programs may be appropriately implemented to manage this high-risk population [9]. Effective and adequate pain management can restore joint function, prevent chronic pain [10], and allow for a more comfortable and rapid rehabilitation [11].

Acupuncture from ancient Chinese medicine is a safe treatment method without serious side effects [12]. It can be used as a complementary and alternative therapy for many diseases such as dyspepsia [13], overactive bladder [14], stress urinary incontinence [15], etc. Clinically, it can also be used as a drug-free intervention to relieve post-operative pain and help reduce the use of opioid analgesics [16]. Post-operative pain control following TKA using acupuncture therapies has more potential to develop into effective treatment regimens than other alternative therapies [17]. Tedesco et al. [16] systematically evaluates and meta-analyses the drug-free interventions available as post-operative analgesia in the context of TKA. Medium-quality evidence shows that electrotherapy and acupuncture after TKA can reduce the use of opioids and delay opioid consumption. Electroacupuncture (EA) can stimulate acupoints to alleviate pain by linking up a painless weak electrical stimulation. EA not only relieves acute pain [18] but is also effective against chronic pain [19]. This may, therefore, be considered as an adjunct intervention for long-term pain relief in standard non-drug therapy. In Mikashima et al.’s study [20], acupuncture on the affected side provided an effective treatment for post-operative acute pain. And in our previous trial [21] on applying EA for post-operative pain management after TKA, the technique of sham EA was mastered. During our study, however, the researchers were concerned that acupuncture near the incision may increase the risk of post-operative infection, so we considered the treatment of opposing needling after operation.

Opposing needling, also known as healthy side acupuncture or contralateral acupuncture, is one of the nine needling methods of acupuncture first recorded in *Huangdi Neijing*. According to the patient’s condition, the needling method is used at select acupoints on the right side of the body when the left side is affected, and vice versa [22, 23]. Opposing needling therapy is used in various types of neuralgia and functional rehabilitation therapies in China [24, 25], wherein acupoints are selected generally on the healthy side corresponding to the affected side [26]. Studies [27, 28] have indicated distinct anti-nociceptive effects and mechanisms between ipsilateral and contralateral acupuncture and moxibustion. And anterior cingulate cortex plays an important role in contralateral acupuncture and moxibustion. Alleviation of pain is one of the major areas for the use of opposing needling; however, it has not been used for the treatment of post-operative pain.

Thus, the study protocol that we designed is a clinical study on the opposing needling method for analgesia and rehabilitation after unilateral total knee arthroplasty.

## Methods/design

### Objective

The aim of this study is to investigate the effectiveness of opposing EA compared with operated side EA or sham EA treatment in patients after unilateral TKA, and to provide clinical evidence for the treatment of post-operative pain by opposing needling.

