### Study design

A randomized, controlled, three-arm, patient- and assessor-blinded trial will be conducted to compare the efficacy of two true EA groups (opposing EA and operated side EA) with a sham EA group (Fig. 1).

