### Sample size

According to the data from the previous preliminary study, through observing the analgesic effect of opposing EA three times after TKA operation, the average VAS score was 37.0 with a standard deviation = 22.6, the average value of sham EA was 46.9, and the standard deviation was 12.5, with a significance level α = 0.05 (two-sided) and power (1 − β) = 0.8. According to the following sample size formula [44, 45], μ is the mean and σ is the standard deviation, κ = n_A_/n_B_ is the matching ratio. τ is the number of comparisons to be made. Look-up table Ζ can be obtained. The sample size was calculated as 96 cases; taking a 15% dropout rate into account, 38 subjects are required in each of the three groups.
$$ {n}_A=\left({\sigma}_A^2+{\sigma}_B^2/\upkappa \right){\left(\frac{Z_{1-\alpha /\tau }+{Z}_{1-\beta }}{\mu_A-{\mu}_B}\right)}^2 $$

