## Discussion

In recent years, with the development of fast-track (FT) surgery for joint problems, clinicians pursue the goals of painless, edema-free, stasis-free, and tubeless rehabilitation management after surgery [46]. For post-operative pain management, we should not only adopt the multi-mode analgesia model [47], but also promote the development of multi-disciplinary [48] approaches, especially by adding the high-quality analgesic methods of traditional medicine and developing the combination of traditional Chinese medicine and modern clinical medicine [49].

This clinical study of opposing needling on analgesia and rehabilitation after TKA is aimed at understanding the feasibility of such a procedure. Under the unified conditions of routine operation mode and routine intraoperative and post-operative analgesic dosage and on the premise of baseline equilibrium of the three groups, three interventions will be given according to each patient’s random number: opposing EA, operated side EA, sham EA.

Acupuncture on the affected side is a conventional non-drug therapy for rehabilitation after TKA [20, 50]. Opposing needling means applying acupuncture on the healthy leg (unoperated) of the patient, where acupoints are selected according to corresponding acupoints and meridian of the operated side. Accumulating evidence from clinical and experimental studies revealed that opposing needling exerts protective and facilitative effects on functional rehabilitation, the underlying mechanism of which remains to be further studied [51]. For patients, needling the healthy side after operation is more convenient and more acceptable. In terms of risk, needling the affected side increases the risk of infection after TKA. At the same time, the opposing needling method avoids the disadvantage of inconvenient selections of acupoints distributed at the surgical site.

In addition to the evaluation of the curative effect during hospitalization, good communication and follow-up with patients will be established. Not only will it help patients physically, but also care for patients psychologically. Through the study, we hope to provide clinicians with high-quality evidence of acupuncture for the recovery of pain and function after TKA and provide more ideas for clinicians in perioperative pain management.

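### The stated sample size and power cover opposing EA versus sham only; the objective's other contrast, opposing versus operated-side EA, is unsized and cannot be reliably answered by the planned difference tests

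*Protocol article*

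**What the plan says.** Three sections of the protocol article describe the comparison of interest, and they differ.

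- **Objective:** the aim is to "investigate the effectiveness of opposing EA compared with operated side EA or sham EA treatment in patients after unilateral TKA". Operated-side EA and sham EA are both comparators for opposing EA, and neither is marked as primary or secondary.
- **Study design:** the trial will "compare the efficacy of two true EA groups (opposing EA and operated side EA) with a sham EA group". Here each true EA arm is set against sham, and no contrast between the two true EA arms is named.
- **Sample size:** for opposing EA, "the average VAS score was 37.0 with a standard deviation = 22.6"; and "the average value of sham EA was 46.9, and the standard deviation was 12.5". These enter a two-mean difference formula "with a significance level α = 0.05 (two-sided) and power (1 − β) = 0.8". No mean, SD, target difference or margin is given for operated-side EA. The formula has a multiplicity term ("τ is the number of comparisons to be made"), but its value is not stated. The result is 96 cases, raised for 15% dropout to 38 in each of the three groups.

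Under Statistical analysis, "Comparisons among the three groups will be analyzed by one-way analysis of variance (ANOVA", with a repeated-measures ANOVA for the primary outcome and significance at 0.05. These are tests of difference. No equivalence or non-inferiority hypothesis appears.

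**The concern.** A single N and a single power figure are given for a three-arm trial whose aim names two comparators, and the inputs concern only one of them. A reader could take the 0.8 as applying to both.

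The contrast left out matters. The Background gives concern about infection near the incision as the reason for turning to opposing needling. The Discussion repeats it ("In terms of risk, needling the affected side increases the risk of infection after TKA") and adds convenience and acceptability. On those motives, a clinician would want to know how much analgesia, if any, is given up by needling the healthy leg. A p-value against zero does not answer that. If the interval is about as wide as the whole assumed benefit over sham, a non-significant result fits both equal analgesia and the loss of most of that benefit.

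**Working it through.** **Inputs from the document (Sample size).** Opposing EA 37.0, SD 22.6; sham EA 46.9, SD 12.5; difference 46.9 − 37.0 = 9.9 mm; two-sided α 0.05; power 0.8; 96 cases, i.e. 96/3 = 32 per arm; 38 per arm after dropout.

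**Assumption.** The document gives no SD for operated-side EA. I take 12.5 to 22.6 mm, the range of the two stated SDs, with their root mean square in between: √((22.6² + 12.5²)/2) = √(667.01/2) = 18.26.

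**Step 1: the plan's own figure.** The printed formula with κ = 1 is n = 667.01 × ((Z + 0.8416)/9.9)², with Z at 1 − 0.05/τ.

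| τ | Z | n per arm |
|---|---|---|
| 1 | 1.645 | 42.1, so 43 |
| 2 | 1.960 | 53.4, so 54 |
| 3 | 2.128 | 60.02, so 61 |

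None gives 32. Only the dropout step reproduces: 32/0.85 = 37.6, so 38.

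**Step 2: power for opposing versus sham at the stated N.** SE = √(667.01/32) = 4.57; 9.9/4.57 = 2.17; power = Φ(2.17 − 1.96), about 58% (57% with the t distribution). At α = 0.05/3 it is 41%. With all 38 per arm it is 66% and 49%.

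**Step 3: opposing versus operated-side EA, one time point.** SE = √((22.6² + s²)/n), where s is the assumed operated-side SD. Half-width = t × SE, with t = 2.00 at 32 per arm and 1.99 at 38. Power is from the two-sample t-test, two-sided 0.05.

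| n per arm | s | SE | 95% CI half-width | power, 9.9 mm | power, 5 mm |
|---|---|---|---|---|---|
| 32 | 12.5 | 4.57 | 9.1 mm | 57% | 19% |
| 32 | 18.26 | 5.14 | 10.3 mm | 48% | 16% |
| 32 | 22.6 | 5.65 | 11.3 mm | 41% | 14% |
| 38 | 12.5 | 4.19 | 8.3 mm | 65% | 22% |
| 38 | 18.26 | 4.71 | 9.4 mm | 55% | 18% |
| 38 | 22.6 | 5.18 | 10.3 mm | 47% | 16% |

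If the two true EA arms are truly equal, the chance at 32 per arm that the interval excludes a loss of 4.95 mm (half of 9.9) is 19% down to 14%.

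**Step 4: allowance for repeated measures.** Averaging m measurements with correlation ρ multiplies the SD by √((1 + (m − 1)ρ)/m). With SD 18.26 in both arms, 32 per arm, m = 3 to 6 and assumed ρ = 0.3 to 0.7, the half-width falls from 8.9 mm to between 5.8 and 8.0 mm. The difference detectable with 80% power falls from 12.8 mm to between 8.3 and 11.4 mm. Power for 4.95 mm rises from 19% to between 23% and 39%.

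**The case against.** **Powering a three-arm trial on its sham contrast is ordinary practice.** The title calls the trial sham-controlled, and the Study design section frames it as true EA against sham. Sizing on opposing versus sham fits that. This stands: leaving the active-versus-active contrast with less power is not an error in itself. The Objective, however, gives both comparators equal standing, and nothing says that the stated power belongs to one of them.

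**No comparability claim is made.** A reader might infer that the investigators intend to treat a non-significant result as proof that the two sites work equally well. The document does not say so, and no equivalence or non-inferiority conclusion is planned. The point is about how a likely result could be read.

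**A two-sided test is a legitimate reading of the aim.** The Background cites different antinociceptive effects of ipsilateral and contralateral needling, and the Objective gives no direction. That is fair. The loss-of-analgesia question is an inference from the stated motives. Even so, a directionless test at this N has low power for any gap much smaller than 9.9 mm.

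**The test is weak, not useless.** It would be too strong to say that the contrast cannot be answered, or that p > 0.05 is the likely result whatever the truth. At a true gap of 9.9 mm, three of the six scenarios in the working have power above 50%, and if both arms had an SD of 12.5 it would be 89%. Repeated measures add some precision. The supported wording is that the tests cannot reliably answer the contrast.

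**Detail may sit in a fuller document.** A contrast hierarchy often does, and its absence is not the finding. The mismatch is between three statements printed in this article.

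**Conclusion.** The point holds as a mismatch of aim, design statement and sizing. The stated N and power do not cover opposing versus operated-side EA. The multiplicity term does not change that, since it can adjust α but supplies no effect for a second contrast. At 32 per arm the single-time-point interval is about ±9 to ±11 mm against an assumed total benefit over sham of 9.9 mm. A gap of half that benefit would usually be missed, even with averaging over repeated measurements.

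The size rests on the assumed operated-side SD of 12.5 to 22.6, on the document's SD of 22.6 for opposing EA and, for the averaging, on assumed correlations. A different operated-side SD would move the figures but not the fact that the contrast is unsized.

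The 0.8 is also not safe for the contrast that was sized: the printed inputs give about 58% at 32 per arm, two-sided 0.05, without multiplicity adjustment.

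**What to change.** 1. Reconcile Objective, Study design and Sample size so that opposing EA versus sham EA is named as the sized contrast.
2. Make opposing versus operated-side EA a secondary estimation comparison in Objective and Statistical analysis. Report the mean VAS difference with its 95% CI, do not decide it by the ANOVA p-value, and state that p > 0.05 will not be read as comparable analgesia. Give the expected half-width (about 9 to 11 mm at 32 per arm, one time point) with its SD assumption.
3. Do not simply attach the stated 0.8 to opposing versus sham. State τ and restate the power from the printed inputs: about 58% at 32 per arm, two-sided 0.05, unadjusted.

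Items 1 and 2 cost wording and one extra reported interval, and need no more patients. Item 3 means printing a lower power than the one now claimed; whether to enlarge the trial for the sham contrast is a separate decision. Sizing the secondary contrast instead would be far more expensive: a 4.95 mm difference at 80% power needs 2 × 18.26² × (2.80/4.95)², about 214 evaluable per arm (101 to 328 for a common SD of 12.5 to 22.6). The downside of estimation is that no claim of comparable analgesia can be made unless the interval itself supports it.
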